**Fig. 2 Fig2:**
[figure not shown]
Schedule of enrolment

### Intervention and control

The REOX study has two arms (see Fig. 2). Both arms included cleansing with saline solution and debridement to remove devitalized tissues, if needed, according to recommendations from clinical practice guidelines.

In the intervention group, the antioxidant dressing will be applied over the wound bed and covered with a secondary adhesive dressing. The dressing will be kept in place for 2 to 3 days, according to the recommendations of the manufacturer.

In the control group (standard practice), a dressing that creates a moist environment will be applied over the wound bed (such as hydrocolloid, alginate, polyurethane foam or silver dressing, according to the nurse’s judgement and the availability of the products at the centre) and covered with a secondary adhesive dressing if necessary. The dressing will be kept in place for 2 to 3 days, according to the recommendations of the manufacturer.

To improve the adherence of the patients to the treatment (both groups), the clinical nurse who treats the patients will reinforce in each dressing change how important it is to keep the dressing in place until the next visit, and explain to the patient that if they are experiencing pain, itching or other wound-related symptoms, they should consult with the nurse but not remove the dressing. Any dressing-related symptoms will be recorded as a possible adverse effect.

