#### Participants

Patients are eligible according the inclusion and exclusion criteria presented in Table 1*.* The sample was recruited from patients with wounds treated in one of the health care centres engaged in the study.

**Table 1 Tab1:** REOX trial inclusion and exclusion criteria

Inclusion criteria	Exclusion criteria
• Patients over 18 years of age • Patients with leg ulcers (venous, ischaemic, traumatic or diabetic foot ulcer) • Patients with dehisced surgical wounds healing by second intention • Patients with pressure ulcers • Wound area between 1 and 250 cm^2^ (wounds larger than 250 cm^2^ are very unusual and outside the scope of this kind of treatment and therefore we decided to exclude it since such a large wound could be more difficult to heal)	• Systemic inflammatory disease or oncological disease • Wounds with clinical signs of infection • Terminal situation (life expectancy less than 6 months) • Ulcers from other aetiologies: tumours, infectious • Wounds treated with negative pressure therapy • Pregnancy • History of sensitivity or allergy to any of the components of the study dressing

In addition, the following criteria for withdrawal from the study will be considered: 1) worsening of the wound according to the clinical judgment of the professional (appearance of clinical signs of infection or others); 2) appearance of allergies or hypersensitivity to the dressing; 3) death; 4) hospital admission that interrupts the treatment in the primary health care centre; and 5) change in the patient’s residence if the new residence is at a different health centre.

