### Randomization and blinding

Patients (*n* = 54) will be randomized into an intervention group (antioxidant dressing) or control group (standard clinical practice using dressings that create a moist environment). The block randomization scheme was generated using the EPIDAT software. Participants will be randomized to receive antioxidant dressing or standard wound dressing with a 1:1 allocation ratio (Fig. 2) using stratified block randomization with a fixed block size per centre. Once the patient has agreed to participate and has been shown to meet the inclusion criteria, the clinical nurse will open opaque closed envelopes sequentially numbered containing a sheet (folded four times) with the group allocation. Neither the patient nor the clinical nurse is blinded to the treatment received; the data and the wound pictures will be codified and the assessor who evaluates the wound pictures and the data analyst will be blinded to the treatment.

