### Outcomes

The primary outcome is the improvement in wound healing with two end points: 1) an increase in the RESVECH 2.0 scale score [37] (score at baseline minus score at 8 weeks); and 2) a reduction in the wound area (area at baseline minus area at 8 weeks). The RESVECH 2.0 score includes the assessment of the wound area, but we also decided to use the reduction in wound area as a specific end point to have a direct measurement of wound size (despite not estimating the sample size with this outcome because there were no data available from previous studies). Additionally, the values at 2, 4 and 6 weeks for each end point will be calculated. These end points are chosen for the clinical relevance of the antioxidant dressing because this product is well-known for removing the nonviable tissue (necrotic or devitalized) in the wound bed, for promoting the production of granulation tissue and for activation of the healing process [35, 42].

The secondary outcomes are the time to achieve a 50% reduction in wound area, the time elapsed until removal of nonviable tissue from the wound bed, reduction of the wound area, the number of completely healed wounds, the pain level and the area of the wound with bacterial load (clinical signs of infection or measurement of surfaces containing bacteria).

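### The one stated adverse-effect rule puts a relatedness judgement before recording in an open-label trial, and death and admission are named only as reasons for withdrawal

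*Protocol article*

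**What the plan says.** Under Intervention and control, patients in both groups who notice pain, itching or another symptom of the wound are told that "they should consult with the nurse but not remove the dressing". The next sentence gives the only adverse-effect rule in the article: "Any dressing-related symptoms will be recorded as a possible adverse effect".

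Under Randomization and blinding: "Neither the patient nor the clinical nurse is blinded to the treatment received". Blinding is confined to two other people: "the assessor who evaluates the wound pictures and the data analyst will be blinded to the treatment".

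Under Participants, the withdrawal criteria include worsening in the professional's clinical judgement (signs of infection among the examples), allergy or hypersensitivity to the dressing, death, and "hospital admission that interrupts the treatment in the primary health care centre". Death and admission appear nowhere else as events to be recorded or compared.

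Under Outcomes, the secondary list begins "The secondary outcomes are the time to achieve a 50% reduction in wound area" and goes on to include pain level and the wound area with bacterial load, which covers clinical signs of infection. Under Data collection and management, RESVECH 2.0, one of the two primary end points, has an infection/inflammation item. Assessments are at baseline and weeks 2, 4, 6 and 8.

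The Data analysis plan has no interim analysis or formal stopping rule, because no harm is anticipated on the strength of a patient series.

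**The concern.** The text moves from symptoms of the wound, which patients should raise, to symptoms of the dressing, which are recorded. Read as written, someone must judge relatedness before an entry is made. Symptoms go to the treating nurse, who knows the allocation and, in the control arm, chose the product from those in routine use. A nurse may be quicker to suspect a new dressing, or slower to blame one expected to help. Either tendency makes the recorded counts differ between arms when the true rates do not.

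The blinded photograph assessor cannot correct this: itching and pain do not show in a picture.

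The rule matters because the Background states that this dressing has not been compared with standard moist dressings. The trial would be a first source of comparative harm data, and it has neither a data monitoring committee nor a stopping rule behind it.

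**Working it through.** The plan gives no figure on harms to reproduce, so the check sets the sections side by side. The one illustration uses assumed rates.

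**1. Is there a filter before recording?** Intervention and control uses a wider class of symptoms for what patients report and a narrower one for what is recorded as a possible adverse effect. The recording sentence is tied to the narrower class. It does not say that other events go unrecorded.

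**2. Who applies it?** The recorder is not named. Symptoms are brought to the nurse (Intervention and control), and one clinical nurse assesses each patient (Data collection and management). That the nurse judges relatedness is a reasonable inference. Patient and nurse are both unblinded.

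**3. What can the filter do?** Let *p* be the true symptom rate, equal in both arms, and *a*₁ and *a*₀ the probabilities that a symptom is attributed to the dressing in the intervention and control arms.

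- Recorded rates: *p* × *a*₁ and *p* × *a*₀. Their ratio is *a*₁ / *a*₀, whatever *p* is.
- Assumed *p* = 0.30, since the documents give no rate:

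| *a*₁ | *a*₀ | Recorded, intervention | Recorded, control | Ratio |
|---|---|---|---|---|
| 0.80 | 0.80 | 0.24 | 0.24 | 1.0 |
| 0.60 | 0.50 | 0.18 | 0.15 | 1.2 |
| 0.80 | 0.40 | 0.24 | 0.12 | 2.0 |
| 0.40 | 0.80 | 0.12 | 0.24 | 0.5 |

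With 27 per group, the third row is 27 × 0.24 = 6.5 against 27 × 0.12 = 3.2 patients. The table shows the mechanism and its two directions, not the size to expect.

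**4. Can infection or worsening be missed although they are in the outcomes?** Dressings stay on for 2 to 3 days and assessments are 14 days apart, so a fortnight holds about 14 / 3 = 4.7 to 14 / 2 = 7 dressing periods. Worsening seen at a change between assessments can lead to withdrawal before the next score. The article mentions no assessment at withdrawal. The Data analysis plan allows the last observation to be carried forward in some cases, which could carry a value from before the event. Its sensitivity analysis uses completed cases, which would leave the patient out.

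**5. What could a harm comparison show at this size?** With 27 per group and assumed true rates, power is about 17% for 20% against 10%, 26% for 30% against 15%, and 45% for 30% against 10%. With no events in 27 patients, the one-sided 95% upper limit is 1 − 0.05^(1/27) = 10.5%. Any harm table would be descriptive, so how the counts are collected matters more than a test on them.

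**The case against.** The strongest case against is that this over-reads a loose sentence. It closes a paragraph on adherence in both groups, covers any such symptom and calls it only a possible adverse effect, which suggests a low threshold. The article condenses a fuller protocol, and the figure listing the variables at each assessment is not shown. Adverse-event definitions, form fields and a safety table may well be there. Their absence here is not a finding.

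Much of that stands, and it rules out several stronger readings:

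- A reader might infer that infection and worsening appear only as withdrawals. They do not: infection is in a secondary outcome and a RESVECH 2.0 item, and worsening enters both primary end points.
- A reader might infer that pain passes through the filter. Pain level is a secondary outcome in its own right.
- A reader might infer that hypersensitivity goes unrecorded. A reaction to the dressing is dressing-related by definition, so its symptoms fall under the stated rule.
- A reader might infer that harms cannot be compared fairly at all. The rule applies to both groups and withdrawals can be counted by arm. The document supports a risk of biased ascertainment and no more.
- A reader might take the 30% loss allowance as patients lost to harm. It is a planning figure for any loss, change of residence included.

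What the objection does not remove is that the one rule the article states is tied to attribution under open treatment, and that death and admission are named only as withdrawal reasons.

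**Conclusion.** The point holds in a limited form. Followed as written, the rule makes recording depend on an unblinded relatedness judgement, so counts of adverse effects may differ by arm through attribution. Death and treatment-interrupting admission are not named as events to compare, and infection or worsening that leads to withdrawal between assessments may escape the scores meant to capture it.

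The size is unknown. It depends on how far the attribution thresholds differ, for which the document gives no basis, and the direction could be either. The conclusion assumes that the treating nurse applies the rule and that the full protocol has no broader one. The calculation of the two primary end points for patients who are assessed is not affected. The change is worth making because it is cheap.

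**What to change.** Reword the sentence under Intervention and control so that every new or worsened symptom and every adverse event is recorded in the same way in both arms, whatever its presumed cause, with attribution to the dressing in a separate field.

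In the Data analysis plan, state that withdrawals will be reported by randomised arm and by reason: worsening or infection, hypersensitivity, admission, death. The withdrawal criteria themselves need no change for this purpose.

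If the full protocol already provides for both, one clarifying sentence is enough.

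The cost is a few form fields at visits that already take place, one descriptive table, and more non-specific symptoms on record. Patients and nurses still report unblinded, so some bias in what is noticed and mentioned will remain.

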### Data collection and management

Participants eligible for study entry will be given a unique, sequential, centre-specific study identifier. Clinical data will be entered into paper-based case report forms. After each assessment, the data will be handled according to internal procedures and stored in a secure server. These files will be backed-up into a password-protected environment. Hard copies will be stored locally, in compliance with the Spanish Data Protection Law (2018).

Each patient included in the study will be assessed by one clinical nurse at baseline and every 2 weeks (weeks 2, 4, 6 and 8). Figure 1 shows the variables collected at each assessment. The follow-up of patients in both groups will be continued until week 8 or until complete healing of the wound if this occurs earlier. A follow-up of 8 weeks was considered adequate for this study since the main action of the antioxidant dressing being evaluated is to reactivate the healing process by avoiding the excess of ROS; according to a previous study published by Castro et al. [35], a significant number of wounds improved by the fourth week. In order to promote participant retention and complete follow-up, the nurse will monitor patients in the health care centre. Furthermore, the principal investigator will have the primary responsibility for study monitoring; a formal data monitoring committee is not considered necessary because there is no access to protected information and there is no personal information recorded.

To monitor wound healing, several variables will be used: 1) wound area by direct measurement of length and width with a graduated ruler (Kundin method) [39]; 2) wound area estimated using digital photography with Helcos software [40, 41]; this software is an integrated wound management system, which allows for estimation of the wound area and the relative percentage of tissue types in the wound bed (granulation, slough and necrotic tissue); and 3) the RESVECH 2.0 scale score for chronic wound healing [37] (this scale assesses six aspects — wound size, depth/affected tissues, wound edges, type of tissue in the wound bed, exudate and infection/inflammation — with a higher score showing more improvement in the healing process from 0 (the worst possible status of the wound) to 35 points (wound healed)).

Other variables that will be recorded are demographic characteristics, anthropometric characteristics, pain level, concomitant medical diagnosis and clinical antecedents, nutritional status, consumption of drugs, tobacco habit, ankle–brachial index and treatment with compressive therapy. No biological specimens will be collected or stored in this study.

### Outcomes

The primary outcome is the improvement in wound healing with two end points: 1) an increase in the RESVECH 2.0 scale score [37] (score at baseline minus score at 8 weeks); and 2) a reduction in the wound area (area at baseline minus area at 8 weeks). The RESVECH 2.0 score includes the assessment of the wound area, but we also decided to use the reduction in wound area as a specific end point to have a direct measurement of wound size (despite not estimating the sample size with this outcome because there were no data available from previous studies). Additionally, the values at 2, 4 and 6 weeks for each end point will be calculated. These end points are chosen for the clinical relevance of the antioxidant dressing because this product is well-known for removing the nonviable tissue (necrotic or devitalized) in the wound bed, for promoting the production of granulation tissue and for activation of the healing process [35, 42].

The secondary outcomes are the time to achieve a 50% reduction in wound area, the time elapsed until removal of nonviable tissue from the wound bed, reduction of the wound area, the number of completely healed wounds, the pain level and the area of the wound with bacterial load (clinical signs of infection or measurement of surfaces containing bacteria).

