#### Sampling

Sample size was estimated based on two possible outcomes. First, to detect a difference of 2 points in the RESVECH 2.0 scale mean scores [37] between the intervention and the control group with a standard deviation of 2.0 (5% type 1 error and 20% type 2 error) based on data published by Castro et al. who found a reduction of 8 points in RESVECH 2.0 at 4 weeks of treatment (this is a 23% reduction) [24]. We used a 2-point reduction for sample estimation as the minimum clinically significant difference, and so the study was powered enough to detect just this small difference. The required sample size for this is 17 patients per group. Second, the time to achieve a 50% reduction of the wound area, estimating an average of 49.5 days in the control group and 30.0 days in the intervention group with a standard deviation of 20.0 days (5% type 1 error and 20% type 2 error), as based on the study by Lee [38]. The required sample size for this is 18 patients per group.

An additional 30% is added to compensate possible loss of patients in follow-up, and so the final sample size is 54 patients (27 patients in each group). It is expected that each one of the three health care centres will recruit 18 patients for the study.

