### Data analysis plan

A researcher who is blinded to group allocation will perform the data analysis. All analyses will be performed with SPPS Statistics software (IBM Corp., Armonk, NY, USA). Data will be expressed as frequency and percentages for categorical variables, and mean, standard deviation, range and median for quantitative variables depending on the distribution (normality will be checked with the Shapiro–Wilk test). The statistical significance level will be set at *P* < 0.05.

For the primary outcome of improvement in wound healing the wound area reduction at 8 weeks in the intervention group compared with the standard care group will be tested by a difference of means test. The increase in RESVECH 2.0 [37] score at 8 weeks between both groups will be examined by a difference of means test (*t* test for independent groups or Mann–Whitney test depending if variables adjust to a normal distribution). The effect size will be estimated by Cohen’s *d* statistic. In addition, a repeated-measures analysis (analysis of variance or Friedman test) and a survival analysis (Kaplan–Meier) will be used to analyse the evolution over time.

For secondary outcomes, proportions and categorical variables will be tested using a chi-squared test, and continuous variables will be tested using a mean difference test (parametric or nonparametric).

Analyses will be performed between groups as randomized (an intention-to-treat analysis). Missing data for the outcomes will be tested if they are missing at random; otherwise the last observation carried forward approach will be used for imputation [43]. Furthermore, sensitivity analyses over all the completed cases (a per-protocol analysis) will be performed to check for inconsistencies.

A subgroup analysis by wound type will also be performed to explore whether the effect of the intervention differs for any type of wound according to its aetiology. Moreover, another subgroup analysis by primary care centre will be carried out to check if there are any differences in outcomes according to the centre.

No interim analyses or formal stop-study rules are planned; no harmful problems are anticipated for patients because this new dressing has been previously tested in a series of patients with wounds of various aetiologies without any serious adverse effects [35].

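### The direction of the RESVECH 2.0 scale is stated both ways, and the primary endpoint's formula contradicts its own label

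*Protocol article*

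**What the plan says.** RESVECH 2.0 is one of two primary endpoints and one of the two bases for the sample size. Its direction comes up in four sections of the protocol article.

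- **Data collection and management** describes the scale "with a higher score showing more improvement in the healing process", running "from 0 (the worst possible status of the wound) to 35 points (wound healed".
- **Outcomes** defines the endpoint as "an increase in the RESVECH 2.0 scale score [37] (score at baseline minus score at 8 weeks". The companion endpoint, in the same sentence, is "a reduction in the wound area (area at baseline minus area at 8 weeks".
- **Data analysis plan** keeps the upward wording: "The increase in RESVECH 2.0 [37] score at 8 weeks between both groups will be examined by a difference of means test".
- **Sampling** gives the design input without a direction, "to detect a difference of 2 points in the RESVECH 2.0 scale mean scores". It then supports that input with an earlier study "who found a reduction of 8 points in RESVECH 2.0 at 4 weeks of treatment (this is a 23% reduction", and adds: "We used a 2-point reduction for sample estimation as the minimum clinically significant difference".

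No section reconciles these statements.

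**The concern.** Label and formula conflict within the Outcomes sentence whatever the true direction of the scale, because baseline minus week 8 is negative whenever the score goes up. Outside that sentence the article is split, so a reader cannot tell which half to correct.

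What is at stake is the sign of a primary result. The between-group mean difference and Cohen's d both carry a sign, and that sign says which dressing did better. The data analyst is blinded to treatment, so group labels would give no warning that the score runs the wrong way. The wound-area endpoint has no such problem, since its label and formula agree. The fault is specific to RESVECH 2.0.

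**Working it through.** **Step 1. Which direction each statement needs.**

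| Statement | Needs |
|---|---|
| Data collection and management: meaning of a higher score | higher = better |
| Data collection and management: anchors 0 and 35 | higher = better |
| Outcomes: the label (*increase*, as improvement) | higher = better |
| Data analysis plan: *increase* | higher = better |
| Outcomes: the formula (baseline minus week 8, as improvement) | lower = better |
| Sampling: 8-point fall in the earlier study | lower = better |
| Sampling: 2-point *reduction* as the smallest difference of clinical interest | lower = better |
| Sampling: 2-point difference between groups, SD 2.0 | neither |

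The first four rows and the next three cannot all hold.

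**Step 2. Is Sampling using the same scale?** 8/35 = 22.9%, which rounds to the stated 23%. The percentage fits a share of the full 35-point range given in Data collection and management, so a different scale length does not explain the conflict.

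**Step 3. The plan's sample size.** Inputs from Sampling: difference 2, SD 2.0, type 1 error 5%, power 80%. Sidedness is not stated, and two-sided is assumed.

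- Normal approximation: n = 2 × (1.96 + 0.84)² × (2.0/2)² ≈ 15.7, rounded up to 16 per group.
- Two-sample t test: n = 16.71, rounded up to 17 per group, which matches the plan.

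The difference enters only through its absolute size relative to the SD, so 17 stands under either orientation.

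**Step 4. The Outcomes formula applied to a patient who improves by 8 points** (illustrative scores).

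| Orientation | Baseline | Week 8 | Baseline − week 8 | Week 8 − baseline |
|---|---|---|---|---|
| Higher = better | 15 | 23 | −8 | +8 |
| Lower = better | 20 | 12 | +8 | −8 |

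The formula gives improvement a positive sign only when lower is better.

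**Step 5. The group comparison if higher is better.** A true advantage of 2 points with SD 2.0 has d = 2/2.0 = +1.0. Under the Outcomes formula the difference is −2 and d = −1.0.

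**Step 6. What a uniform flip leaves alone.** One simulated data set used 27 patients per group, true mean gains of 8 and 6, and an SD of change of 2.

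| Change score | Mean difference | Cohen's d | t-test p | Mann–Whitney p |
|---|---|---|---|---|
| Week 8 − baseline | +2.18 | +1.22 | 0.000043 | 0.000086 |
| Baseline − week 8 | −2.18 | −1.22 | 0.000043 | 0.000086 |

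Only the signs differ.

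**The case against.** The strongest defence is that little of the inference depends on this. A consistent sign flip leaves the two-sided p-values, the power and the sample size as they are, and the design input in Sampling has no direction. This stands.

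The protocol also holds a partial safeguard. Wound area is correctly oriented and is itself a component of RESVECH 2.0. If wounds shrink on average while the RESVECH change appears to worsen, an analyst can notice without knowing the allocation. That makes an unnoticed reversal less likely, but it does not tell the analyst which statement to follow.

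A reader might infer three stronger things that the document does not support.

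- *That benefit will be read as harm.* The negative score follows only if the published scale description is applied. If lower is better, the formula behaves properly. The supportable word is *could*.
- *That patients who heal early may be coded to the wrong end of the scale, an error of 35 points each.* Follow-up does stop at complete healing, but the article has no rule that assigns these patients an anchor value. The nurse's own assessment could supply the score.
- *That completed forms have been scored inconsistently.* The case report form is not shown and nothing in the article indicates this.

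**Conclusion.** The contradiction is real and can be seen from the article alone. A primary endpoint has a formula that opposes its own label, and its direction of benefit is stated both ways across four sections. It should be corrected before analysis.

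The size of the problem depends on the true orientation. If scores follow Data collection and management, the signs of the mean change, the group difference and Cohen's d all reverse: +8 becomes −8, +2 becomes −2, and d goes from +1.0 to −1.0 at the planning values. If lower is better, the formula needs no change, and the errors are the anchors, the description of a higher score, and the word *increase* in Outcomes and in the Data analysis plan. The article does not settle which case applies. In neither case do the two-sided p-values, the power or the 17 per group change, provided every score is oriented the same way.

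**What to change.** Confirm the orientation from the scoring sheet in the case report form and from the cited instrument, then use it throughout.

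- **If lower is better:** correct Data collection and management so that 0 is the healed wound, 35 the worst status, and a lower score means improvement. Keep baseline minus week 8, and call the endpoint a decrease in Outcomes and in the Data analysis plan.
- **If higher is better:** keep Data collection and management, change the Outcomes formula to week 8 minus baseline, and correct the direction wording in Sampling for both the 8-point and the 2-point figures.

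In either case, state once which sign of the group difference favours the antioxidant dressing. As a precaution, check that forms completed since recruitment began in September 2019 were scored in one direction at all three centres.

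The cost is a wording amendment and a check of scores already entered. No patients, visits or procedures are added, and the sample size does not change.

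### Clinical signs of infection are both a component of a secondary outcome and a named trigger for withdrawal, and the stated missing-data handling under-records them

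*Protocol article*

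**What the plan says.** Four parts of the protocol article bear on this.

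- **Participants.** The exclusion criteria in Table 1 include "Wounds with clinical signs of infection". Below the table, "the following criteria for withdrawal from the study will be considered", and the first is "worsening of the wound according to the clinical judgment of the professional (appearance of clinical signs of infection or others".
- **Data collection and management.** Each patient is "assessed by one clinical nurse at baseline and every 2 weeks (weeks 2, 4, 6 and 8", and follow-up "will be continued until week 8 or until complete healing of the wound if this occurs earlier". Withdrawal is not mentioned there as a reason for follow-up to end.
- **Outcomes.** One of the secondary outcomes is "the area of the wound with bacterial load (clinical signs of infection or measurement of surfaces containing bacteria".
- **Data analysis plan.** "Analyses will be performed between groups as randomized (an intention-to-treat analysis". Missing outcome data are to be tested for being missing at random, with LOCF if they are not. Completed cases form a sensitivity analysis.

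The article does not say that a withdrawal for infection counts as an outcome event. Nor does it say whether an assessment is made at withdrawal, or whether withdrawn patients are still followed.

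**The concern.** On the clinical-sign component every patient enters free of the event, and a patient who develops it meets a criterion for leaving the study. The event and the loss of the patient's later data then tend to coincide. If the analysis rests on scheduled values, with LOCF or completed cases for the rest, infections that led to withdrawal can be entered as no infection or disappear from the comparison.

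This outcome bears on safety in a trial without a data monitoring committee. It also bears on the possible antibiofilm activity given in the Background as part of the rationale. Silver dressings are allowed in the control arm, so a true difference in either direction is plausible. A difference that shows only in a listing of withdrawals would be easy to miss.

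**Working it through.** **Group size.** The plan's figure of 27 per arm is used below, so it was checked first. For two means, n per group = 2(1.96 + 0.84)² × (SD/difference)², which gives:

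- RESVECH 2.0 (difference 2, SD 2.0): 15.7, so 16; the exact t-test version gives 16.71, so 17, as stated.
- Time to 50% area reduction (difference 49.5 − 30.0 = 19.5 days, SD 20.0): 16.5, so 17; the t-test version gives 17.53, so 18, as stated.
- Loss allowance: 18/(1 − 0.30) = 25.7, so 26, against 27 stated. The gap is immaterial here.

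**What the stated rules do to a patient who develops signs and is withdrawn.**

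1. *Signs first seen at a scheduled assessment.* The visit can record them, and LOCF would carry that record forward. The event is kept.
2. *Signs first seen between scheduled assessments.* The last recorded value predates the infection. The later values are missing because of the event itself, which is the situation for which the plan names LOCF. LOCF then enters the patient as free of infection.
3. *Completed-case analysis.* The patient is dropped in either case.

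**How often case 2 could arise.** Dressings stay in place for 2 to 3 days (Intervention and control), and outcomes are assessed every 14 days. That gives 14/3 = 4.7 to 14/2 = 7 dressing changes per interval, of which one can coincide with an assessment. Assuming that onset is noticed at a random dressing change, the share noticed off schedule is 1 − 1/4.7 = 79% to 1 − 1/7 = 86%.

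**Illustration with assumed infection rates.** The document gives none. Expected infections per arm = 27 × rate; those noticed off schedule = that number × 0.79 to 0.86.

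| Assumed 8-week rate | Infections per arm | Noticed off schedule |
|---|---|---|
| 10% | 2.7 | 2.1–2.3 |
| 20% | 5.4 | 4.2–4.6 |
| 30% | 8.1 | 6.4–6.9 |

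The last column is the number that LOCF would enter as uninfected if every such patient were withdrawn. It is an upper bound under these assumptions, because withdrawal rests on judgment.

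**Power if every infection is counted.** Power = Φ{(|p₁ − p₂| − 1.96 √[2p̄(1 − p̄)/27]) / √[(p₁(1 − p₁) + p₂(1 − p₂))/27]}, with control and intervention rates assumed:

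- 10% v 5% (2.7 v 1.4 events): (0.05 − 0.1405)/0.0714 = −1.27; power 10%.
- 20% v 10% (5.4 v 2.7 events): (0.10 − 0.1905)/0.0962 = −0.94; power 17%.
- 30% v 10% (8.1 v 2.7 events): (0.20 − 0.2134)/0.1054 = −0.13; power 45%.

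Complete counting removes the under-recording but does not make the comparison well powered.

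**Direction.** Randomization and blinding states that the clinical nurse knows the treatment. The withdrawal criterion leaves the decision to the judgment of an otherwise unspecified professional. If knowledge of the dressing affects who is withdrawn, the loss differs by arm, and its direction cannot be told from the document.

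**The case against.** A reader might infer that patients leave before the infection can be measured, that the outcome is emptied in both arms, and that a real difference would show as nought against nought. The document does not support this, for these reasons:

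- Withdrawal is triggered by someone seeing the signs, so the event is observed; what is missing is a rule that it counts.
- The criteria are to be considered, and the first depends on clinical judgment, so not every infected patient need leave.
- The outcome has a second component, measurement of surfaces containing bacteria, which is neither an exclusion nor a withdrawal trigger. The Background says that over 90% of chronic wounds carry biofilm, so bacterial load is not zero at entry.
- Week 8 is fixed only for the primary end points, and the main analysis is as randomised.

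It can also be said that an event may properly be both an outcome and a reason for leaving, and that a condensed article may leave the counting rule to a fuller document. Part of this stands: the two roles are not incompatible in themselves. But the article goes beyond silence. It states LOCF and a completed-case analysis, and applied as written these enter or drop infected patients in the wrong way. An as-randomised analysis set does not repair a value carried forward from before the infection.

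Finally, infection is also scored within RESVECH 2.0, which covers "type of tissue in the wound bed, exudate and infection/inflammation". That is no substitute, because the scale is recorded at the same visits and is lost at the same withdrawals.

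**Conclusion.** The point holds in limited form. Clinical signs of infection are excluded at entry, named as a trigger for withdrawal, and used as one of two components of a secondary outcome. Under the stated LOCF and completed-case rules this component is under-recorded, and possibly unevenly between arms because the nurse is unblinded. The conclusion rests on some infections appearing between scheduled visits and leading to withdrawal without a recorded assessment.

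The size is unknown. The 3 to 8 infections per arm, and the 79–86% noticed off schedule, depend on assumed rates and on onset noticed at a random dressing change. The effect is on one secondary outcome without its own sample-size basis, so this should be corrected but does not threaten the trial. The same withdrawals also remove week-8 values of both primary end points, which is a further reason to settle what data are collected after withdrawal.

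**What to change.** 1. Analyse the clinical-sign component as occurrence of clinical signs of infection by week 8 in all randomised patients, by arm. Count withdrawal for infection as an event, and do not impute this component by LOCF.
2. Record an outcome assessment at withdrawal and, where the patient agrees, the remaining scheduled assessments.
3. Report bacterial surface measurement separately from clinical signs.
4. Reconcile Participants, Data collection and management, Outcomes, and Data analysis plan on what withdrawal from the study means for data collection. How infection is managed, and when a patient is withdrawn, is for the sponsor to state; no change to it is proposed.

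The cost is some wording, a reason-for-withdrawal field and a few extra routine assessments. Power for this outcome stays low at 27 per arm (about 10% to 45% in the scenarios above), so it is best reported as counts and proportions with confidence intervals.
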